## Abstract

**Introduction:**

Knee osteoarthritis is a leading cause of pain and disability and frequently results in total knee arthroplasty (TKA). Decisions about surgery and postoperative management rely largely on subjective pain scales and patient-reported outcome measures (PROMs), and 10–15% of patients remain dissatisfied after TKA despite technically successful surgery. Evidence suggests that pain is partly reflected in peripheral immune signalling, yet this neuroimmune interface has not been studied in patients with joint pain due to knee osteoarthritis. This study will explore whether peripheral immune responses (interleukin-1 beta, IL-1β) are associated with pain and may serve as objective pain biomarkers in patients with painful knee osteoarthritis compared with pain-free controls and how these markers relate to pain and psychological (anxiety, depression and pain catastrophising) PROMs. This will be the first study to correlate pain markers (peripheral immune responses) with subjective pain levels in orthopaedic patients with symptomatic knee osteoarthritis.

**Methods and analysis:**

This is a protocol for a prospective cross-sectional matched-subject observational study. We will include 20 adults undergoing unilateral primary TKA for painful advanced knee osteoarthritis, their contralateral pain-free knees as internal controls and 20 age and sex matched healthy controls without joint pain or functional limitation. All participants will undergo standardised clinical assessment and complete pain and psychological PROMs. In patients with TKA, venous blood will be collected pre-operatively. During TKA surgery, synovial fluid will be aspirated from the painful operated knee and the contralateral pain-free knee. Healthy controls will provide a single venous blood sample at a hospital visit. Peripheral blood mononuclear cells and synovial fluid mononuclear cells will be stimulated ex vivo with toll-like receptor 2 and 4 agonists to quantify IL-1β release. In parallel, hyperspectral imaging will characterise unstimulated immune cell phenotypes. Multivariable statistical and machine-learning approaches will relate biomarker profiles to pain and psychological PROMs.

**Ethics and dissemination:**

The study has been approved by the Southern Adelaide Local Health Network (SALHN) HREC (references: 2024/HRE00253, SSA 2024/SSA00641). Written informed consent will be obtained from all participants. Study results will be disseminated through peer-reviewed publications and presentations at national and international scientific conferences.

**Trial number registration:**

ACTRN12626000084381.

STRENGTHS AND LIMITATIONS OF THIS STUDYIntegration of immune signatures with subjective pain and psychological health, and inclusion of both synovial fluid and peripheral blood immune responses to characterise local and systemic inflammatory activity.The matched-subject design using the contralateral pain-free knee as an internal control reduces inter-individual biological variability and strengthens causal inference regarding pain-related immune responses.Standardised sample handling, stimulation protocols and centralised laboratory analyses enhance reproducibility, while blinding of laboratory investigators to clinical status minimises measurement bias.Strict eligibility criteria and exclusion of comorbid conditions that affect immune activity improve internal validity but may limit generalisability to more complex, multimorbid arthroplasty populations.Absence of radiographic confirmation of osteoarthritis in asymptomatic controls may allow subclinical disease, potentially biasing results towards the null and underestimating true pain-biomarker associations.

## Introduction

 Knee osteoarthritis is one of the most prevalent chronic degenerative joint disorders globally and represents a leading cause of pain, functional decline and disability.^1^ Total knee arthroplasty (TKA) is a well-established intervention, designed to relieve pain and restore mobility.^2^,^4^ However, postoperative outcomes remain variable and not universally satisfactory. Approximately 10–15% of patients with TKA report persistent pain or dissatisfaction following surgery, despite otherwise successful radiographic and functional results.^5^,^9^ A considerable contributor to this variability is the inherently subjective nature of pain assessment, which relies predominantly on patient-reported scores such as the Visual Analogue Scale and Numerical Rating Scale (NRS). While these measures are clinically practical, they are influenced by psychological state, personality traits and contextual factors, potentially obscuring the true biological driver of pain.^10^,^12^ Literature also suggests that preoperative patient-reported pain intensity prior to TKA is only moderately related to radiographic knee osteoarthritis severity^13^,^17^ and mostly related to female sex and psychological symptoms including anxiety, depression and pain catastrophising symptoms.^18 19^ This creates uncertainty in pain evaluation and decision-making regarding the timing and necessity of joint replacement surgery, and complicates the interpretation of recovery trajectories.

Growing evidence over the past two decades has revealed that pain perception is not exclusively a central nervous system phenomenon but arises from a bidirectional neuroimmune interface in which peripheral immune activity mirrors and modulates nociceptive processing in the brain.^20^ Animal and human studies have demonstrated the involvement of glial activation,^21^,^24^ Toll-like receptor (TLR) expression and peripheral cytokine release in chronic pain pathways.^25^,^27^ In individuals with dysmenorrhoea and other chronic pain states, stimulated immune responses, particularly interleukin-1β (IL-1β) release from peripheral blood mononuclear cells, were found to be substantially elevated compared with pain-free controls.^28 29^ These findings suggest that inflammatory signatures may serve as objective biomarkers of pain intensity. Despite this progress, no studies to date have explored whether similar immune responses occur in somatic pain conditions such as osteoarthritis-related knee pain. This represents a critical knowledge gap, given that osteoarthritis pain is clinically heterogeneous: some patients report severe pain despite minimal radiographic degeneration, whereas others with advanced joint damage experience surprisingly low symptom burden.^30 31^ Objective pain biomarkers could provide insight into this discrepancy, supporting more personalised surgical decision-making and postoperative care and pain management.

The primary aim of this exploratory study is to investigate whether peripheral immune responses, IL-1β expression quantified from both peripheral blood mononuclear cells (PBMCs) and synovial fluid mononuclear cells (SFMCs), differ between patients with symptomatic knee osteoarthritis awaiting TKA and pain-free healthy controls. We hypothesise that stimulated immune responses (IL-1β release) are elevated in patients with symptomatic knee osteoarthritis compared with pain-free controls. Secondary exploratory analyses will (1) examine associations between immune responses, subjective pain measures and psychological factors and (2) evaluate hyperspectral (HS) imaging as a complementary approach for characterising immune cell phenotypes.^32^ This study is intended as a hypothesis-generating study to inform future research on objective pain biomarkers in orthopaedic populations, and to address the absence of objective, biologically anchored pain measurement in orthopaedic surgery. This exploratory study applies neuroimmune biomarker technology to musculoskeletal pain, and may provide a foundation for integrating objective biological markers with subjective pain assessment to improve clinical decision-making and ultimately contribute to a more multidimensional approach of pain assessment.

## Methods and analysis

### Aim, design and setting of the study

This study concerns an exploratory cross-sectional matched-subjects observational study and will be performed in accordance with the Declaration of Helsinki guidelines, and reported in accordance with Strengthening the Reporting of Observational Studies in Epidemiology (STROBE) guidelines. All aspects of this study have been approved by the Southern Adelaide Clinical Human Research Ethics Committee (SAC HREC), Southern Adelaide Local Health Network (SALHN) (2024/HRE00253). Trial registration at the Australian and New Zealand Clinical Trials Registry was completed before commencement of participant recruitment and enrolment (Trial Registration Number: ACTRN12626000084381, date: 22–01-2026. Universal Trial Number: U1111-1332-7067).

Recruitment is planned to commence in March 2026 and is expected to continue for approximately 6 months. Laboratory analyses will be performed in batches during and after recruitment. The investigators performing the laboratory analyses are blinded to the clinical status of the patients. Participant enrolment, clinical assessments, and sample collection will be conducted in Noarlunga Hospital (Flinders Medical Centre), Adelaide. Investigators will not be blinded to group allocation (group with patients awaiting TKA or group with healthy controls). Sample analyses and data analyses will be performed in the Neuroimmunopharmacology Laboratory of Helen Mayo South Building, University of Adelaide.

The primary aim of this exploratory study is to assess whether peripheral immune response parameters (IL-1β release following TLR-2 and TLR-4 activation) differ between painful osteoarthritic knees and pain-free controls. This will be conducted through measuring peripheral immune responses (pain biomarkers, ie, IL-1β expression), quantified from both PBMCs and SFMCs following TLR-2 and TLR-4 activation using PAM3CSK4 (PAM3, a synthetic lipopeptide which functions as an agonist for TLR-2) and lipopolysaccharide (LPS, ie, endotoxin, gram-negative bacterial cell wall component which functions as an agonist for TLR-4), between patients with symptomatic knee osteoarthritis awaiting TKA and pain-free healthy controls.

Secondary exploratory aims include (1) assessing associations between immune responses (IL-1β expression) and subjective pain scores, (2) exploring relationships between immune responses and psychological factors (anxiety, depression, pain catastrophising) and (3) evaluating HS imaging as a complementary approach for characterising immune cell phenotypes by assessing the relationship between HS imaging hues and IL-1β expression.

### Patient and public involvement

Patients and the public were not involved in the design of this study, including the development of the research question, outcome measures, study design or recruitment strategy. The study was designed based on identified gaps in objective pain assessment in osteoarthritis and feasibility within standard clinical care pathways. Participants are not scheduled to be involved in the conduct of the study. Results will be disseminated via peer-reviewed publication and scientific presentations. Where feasible, a summary of the study findings will be made available to participants on request.

### Participants and eligibility criteria

Participants will be consecutively included after screening for eligibility and provided informed consent at the orthopaedic clinic of Noarlunga Hospital, Flinders Medical Centre, SALHN. The study planned to enrol 3 groups of participants: (1) 20 patients awaiting TKA including 20 *painful* knees with moderate to severe osteoarthritis, (2) 20 controls, the healthy contralateral *pain-free* knee of these 20 patients awaiting TKA and (3) 20 different healthy controls for venous blood measurements, age and sex matched healthy individuals with no pain complaints in general at that moment, and no function limitation or pain in any joint (no diagnosed osteoarthritis in both knees). This will result in 40 participants in total: Group 1: 20 patients with 20 *painful* knees with osteoarthritis that are awaiting TKA and 20 *pain-free* contralateral control knees of the same patients; Group 2: 20 *pain-free* control patients without any knee complaints.

Healthy controls are defined as individuals without knee pain or functional limitations in either knee. Radiographic imaging will not be performed in this group, as the primary focus of the study is the biological correlates of pain rather than structural osteoarthritis, and obtaining radiographs in asymptomatic individuals solely for research purposes would expose participants to unnecessary radiation. It is acknowledged that some asymptomatic individuals may have radiographic osteoarthritis; however, structural changes and pain symptoms are known to correlate only moderately.^13^,^17^

Inclusion criteria for eligibility for this study are (1) awaiting a unilateral primary TKA for symptomatic (painful) advanced osteoarthritis,^33^ (2) asymptomatic (pain-free) contralateral knee without functional limitation or pain (no or mild osteoarthritis), (3) otherwise good general health, (4) aged 18 years or over, (5) completion of all preoperative questionnaires and (6) providing informed consent.

Exclusion criteria for all subjects include (1) TKA indication other than symptomatic osteoarthritis for painful knee, (2) painful osteoarthritis in any other joint, (3) other relevant pain complaints elsewhere, (4) presence of any auto-immune diseases, for example, rheumatoid arthritis, lupus, inflammatory bowel disease, psoriasis, etc, (5) one or more of the following comorbidities: diabetes, gout or septic or reactive arthritis in any joint or any clinically significant renal, hepatic, cardiac disease, (6) a medical history including: fracture or surgery to either of the knees, recent (<3 months) major surgery or significant trauma, (7) presence of an inflammatory process, or clinically significant infection in the last 4 weeks, (8) immunisation within the last 4 weeks, (9) current use of immunosuppressant medication such as a steroid, hydroxychloroquine, methotrexate or azathioprine, (10) inability to read or comprehend the written information provided, (11) current use of medications known to affect innate immune responsiveness including amitriptyline, chemotherapy or Tumor Necrosis Factor Alpha (TNF-α) inhibitors or (12) current pregnancy.

### Recruitment and enrolment procedures

Initial recruitment of 20 patients awaiting a unilateral primary TKA for symptomatic (painful) advanced osteoarthritis at Noarlunga Hospital—SALHN will be via knee arthroplasty surgeons at the orthopaedic department. The recruitment of the 20 healthy controls without knee symptoms in both knees will also be performed via knee arthroplasty surgeons at the orthopaedic department of Flinders Medical Centre and Noarlunga Hospital.

All of these patients will be approached by email, which will include links to the study information. An additional email will be sent to all interested patients willing to participate, including the informed consent form, and a more detailed overview of the study.

For all participants who complete informed consent, eligibility will be reviewed through the electronic health-record system according to the inclusion and exclusion criteria, and baseline patient demographics (age, gender, body mass index [BMI], smoking, American Society of Anesthesiologists (ASA) physiological status classification, side of painful and pain-free control knee and other comorbidities) and preoperative medication, specifically pain medication, will be collected. Subsequently all patients (n=40) will be contacted by phone to confirm the presence and absence of all inclusion criteria and exclusion criteria, respectively.

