### Data analysis plan

Primary analyses aim to assess whether peripheral immune response parameters differ between painful osteoarthritic knees and pain-free controls. This will be evaluated using both within-subject comparisons (painful knee vs contralateral pain-free knee in patients undergoing TKA for synovial fluid analyses) and between-group comparisons (patients vs healthy controls for peripheral blood analyses). Secondary analyses will explore associations between immune response parameters and PROMs for pain intensity and psychological factors including anxiety, depression and pain catastrophising. All secondary analyses, including multivariable and machine-learning approaches, are exploratory in nature and aimed at hypothesis generation rather than confirmatory inference.

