#### Primary outcome analysis: painCELL data

Concentration-response curves from the in vitro innate immune stimulated IL-1β release from PBMCs and SFMCs are calculated using GraphPad Prism version 8 (MathWorks; Natick, Massachusetts, USA). Differences between pain-free controls and painful symptomatic osteoarthritis patients (within the same patient for synovial fluid samples and a different patient for blood samples) will be assessed on EC_50_, Hillslope and ‘Top’ (or E_max_). The ‘Bottom’ value will be constrained to a constant of 0. An F-test in GraphPad Prism will be performed to determine if these values should be the same or different between the participant groups. The goodness of fit obtained from the TLR-2 stimulation is not sufficient to warrant presentation in the results, owing to lower-than-expected cytokine expression in the assays.

The painCELL assay cytokine data will be combined with osteoarthritis severity and NRS-pain reports, as well as other demographics (such as mental state) for each participant in a data file. Additional parameterisation of the data set will be performed to capture the delta change in cytokine release between low and high concentration innate immune challenges and between these delta values and the steepness of the concentration response.

First, a feature selection (dimensionality reduction) step will be performed to remove highly correlated variables, by examining the correlation matrix and applying the ‘Bivariate Correlations’ function to identify and exclude variables with Pearson Correlation coefficients greater than 0.8. For each specific hypothesis test, data subsets will be created using the ‘Select Cases’ function to exclude irrelevant subject data (eg, when testing the model for Healthy synovial sample Controls and the contralateral painful knee, Healthy blood sample Controls data will be excluded).

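### Pain medication is collected but has no stated role in the blood comparison or the IL-1β–NRS association, so a drug effect could mimic or mask a pain effect

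*Protocol article*

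**What the plan says.** All references are to the protocol article.

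- **Recruitment and enrolment procedures.** At the record review, "preoperative medication, specifically pain medication, will be collected". It is listed after the bracketed demographics and apart from them.
- **Participants and eligibility criteria, exclusions.** Criterion 9 removes "current use of immunosuppressant medication such as a steroid, hydroxychloroquine, methotrexate or azathioprine". Criterion 11 removes "current use of medications known to affect innate immune responsiveness including amitriptyline, chemotherapy or Tumor Necrosis Factor Alpha (TNF-α) inhibitors". Neither names anti-inflammatory drugs, opioids or any other analgesic class.
- **Participants and eligibility criteria, controls.** These are "age and sex matched healthy individuals with no pain complaints in general at that moment". Medication is not a matching factor.
- **Data analysis plan.** Synovial fluid is compared within patients, painful knee against pain-free knee. Blood is compared between patients and different, healthy people.
- **Primary outcome analysis: painCELL data.** "An F-test in GraphPad Prism will be performed to determine if these values should be the same or different between the participant groups". No covariate is mentioned. The cytokine data are then "combined with osteoarthritis severity and NRS-pain reports, as well as other demographics (such as mental state) for each participant".
- **Secondary aims and Sample size calculation.** The association of IL-1β with pain scores is a secondary exploratory aim. Covariates in secondary models are kept few, with one psychological variable per model.

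The strengths and limitations list does not mention medication.

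**The concern.** In blood, the reason to take an analgesic goes with group membership: patients have a painful knee, and controls are chosen for having no pain. Criterion 11 shows that the protocol itself accepts that concomitant drugs can change the quantity being measured. If some patients take such a drug and controls do not, the by-group difference mixes pain with its treatment.

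The IL-1β–NRS association has a second difficulty. Treatment may lower the recorded NRS, may be used more by those in worse pain, and may act on IL-1β release, so the distortion can go either way.

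At stake is the study's central inference, that stimulated IL-1β release is an objective marker of pain. A hypothesis carried forward to a larger study could be about a drug, or a real pain signal could be hidden by one.

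**Working it through.** **1. The plan's own figure.** Inputs from the Sample size calculation: difference 2.40, SD 1.78, 5% type 1 error (taken as two-sided), 90% power.

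n per group = 2 × [1.78 × (1.960 + 1.282) / 2.40]² = 11.56, rounded up to 12, or 24 in total. This matches the stated figure. With 20 per group, power for 2.40 is 98.6% (noncentral t). The sample size is not in dispute.

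**2. What a drug effect could do to the blood comparison.** The documents give no usage rates and no drug effect, so the following are assumptions: a fraction f of patients and no controls use a drug that shifts EC50 by s SDs, and there is no true pain effect.

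- Bias = f × s × 1.78.
- Patient SD = 1.78 × √(1 + f(1 − f)s²); control SD = 1.78.
- Rejection rate: two-sample t-test, 20 per group, 38 df, noncentrality = bias / √(patient SD²/20 + 1.78²/20).

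| f | s | Bias | Bias / 2.40 | Rejection at nominal 5% |
|---|---|---|---|---|
| 0.4 | 0.5 | 0.36 | 15% | 9.3% |
| 0.6 | 0.5 | 0.53 | 22% | 14.9% |
| 0.6 | 1.0 | 1.07 | 45% | 41.6% |
| 0.8 | 0.5 | 0.71 | 30% | 23.1% |
| 0.8 | 1.0 | 1.42 | 59% | 66.0% |

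Allowing some use among controls changes little. With 80% against 10% users, a 0.5 SD shift gives a bias of 0.62 and 18.6% rejection, and a 1 SD shift gives 1.25 and 53%. For a drug alone to produce the whole 2.40 at those rates, the shift would have to be 2.40 / 0.70 = 3.4 units, about 1.9 SD.

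**3. Why a covariate in the two-group model is not the answer.** Use and group nearly coincide. With p₁ and p₀ the user fractions and p̄ their mean, φ² = [(p₁ − p₀)/2]² / [p̄(1 − p̄)], and the variance of the group effect is multiplied by 1/(1 − φ²). Power for 2.40 with 20 per group and 37 df becomes:

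- 60% vs 10% users: φ² = 0.275, factor 1.38, power 94%
- 80% vs 10%: φ² = 0.495, factor 1.98, power 84%
- 90% vs 5%: φ² = 0.724, factor 3.63, power 59%
- 100% vs 0%: not estimable

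**4. What a restricted comparison could show.** At 40–80% use, 20 × (1 − f) = 12 to 4 patients are non-users. Against 20 controls, with SD 1.78, SE = 1.78 × √(1/m + 1/20) for m non-users:

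| Non-users | SE | 95% CI half-width | Power for 2.40 |
|---|---|---|---|
| 12 | 0.65 | 1.33 | 95% |
| 8 | 0.74 | 1.53 | 87% |
| 4 | 0.97 | 2.02 | 65% |

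The restricted comparison is informative unless very few patients are analgesic-free.

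**The case against.** **This belongs in an analysis plan that is not shown.** In part this stands: an unseen plan may give medication a role. But the article does state its blood test, the contents of its data file and its covariate limit, and the point concerns those statements.

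**A reader might infer that analgesics are permitted.** The documents do not say so. Criterion 11 describes an open class, and some analgesics may fall within it. The supportable statement is that no analgesic class is named. Collecting pain medication may also serve the eligibility check, although singling it out suggests that users are expected among those enrolled.

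**A reader might infer that medication is left out of the analysis file.** The wording does not settle this. The list there is open, and it counts mental state as a demographic although the enrolment section does not. Even if medication is in the file, the by-group F-test as described does not use it.

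**The magnitude is assumed.** This stands. The rejection rates also come from a t-test on one EC50 per participant, not from the planned F-test on fitted curve parameters. The direction is unknown too: a drug effect opposite to the hypothesised rise in IL-1β release would mask a pain effect.

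**The study is exploratory, and half of the primary analysis is within patients.** Both are true. Systemic medication is common to both knees of a patient, so the synovial comparison is largely protected. This narrows the point to blood and to the NRS association.

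**Restriction and adjustment have their own bias.** This also stands. Use depends on pain, so non-users may be milder cases, and an analgesic indicator may condition on a consequence of pain. Both are sensitivity analyses, not cures.

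**Conclusion.** The concern holds for the blood comparison and for the IL-1β–NRS association. As written, neither can separate pain from its treatment, although relevant information is being collected. The step from the text to probable enrolment of users, mostly among patients, is an inference from the control definition, criterion 11 and the collection of pain medication; no usage rates are given.

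The figure of about 9–66% false rejection (bias 0.36–1.42 EC50 units) illustrates what is possible under the assumed use and shift. It is not an estimate for this study. A reader might conclude that the blood result will be biased towards a pain effect, but the documents do not show that any enrolled patient's analgesic changes IL-1β release, or in which direction. The point merits a change before analysis begins; it does not invalidate the design.

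**What to change.** Keep the primary comparison as it is. Using the medication data already planned:

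1. Within patients, report the IL-1β parameters by analgesic class (anti-inflammatory, opioid, adjuvant, none).
2. Pre-specify a sensitivity analysis of patients not using analgesics against controls. Report its estimate and confidence interval beside the main result. Do not set a rule that both must point the same way, since chance alone meets it about half the time when there is no effect.
3. Report the IL-1β–NRS association within patients with and without a single analgesic-use indicator, labelled as sensitivity only because use depends on pain. By the protocol's guide of 10 patients per covariate, NRS and this indicator take up the two terms that 20 patients allow, so this model has no room for a psychological variable.
4. If the estimates diverge, or the restricted one is too imprecise, limit the blood conclusion to pain or its treatment.

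The cost is a few sentences of analysis text. The restricted analysis is smaller and may compare milder cases with controls, which should be said when it is reported. Recording last intake at the blood draw is optional and would be new data: one question at a visit already scheduled. No change to any patient's medication is proposed.
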